### Statistical considerations

The primary objective is to assess whether adaptive radiotherapy techniques when delivered at multiple centres can lead to a reduction in the level of acute non-GU toxicity experienced by patients with MIBC unsuitable for daily radical radiotherapy.

The sample size is based on the primary endpoint of acute (up to 3 months after the end of radiotherapy) non-GU CTCAE >grade 3 toxicity. An A’Hern exact phase II design was used to rule out an upper limit for each planning method separately. Based on results of the non-randomised single centre phase II feasibility study of adaptive predictive planning for hypofractionated bladder radiotherapy (APPLY study; NCT01000129),^18^ it is expected that the acute non-GU >grade 3 rate will be 10% (p1=0.9) in patients receiving adaptive planning. The study is designed to rule out a 30% (p0=0.7) upper limit of >grade 3 non-GU toxicity with each planning method. For 80% power (β=0.2)and 5% alpha (one-sided) in each planning group, 28 evaluable patients are required and if 5 or more experience non-GU >grade 3 toxicity, then the acute toxicity associated with that planning technique will be assumed to be too high. To be evaluable for acute toxicity, participants must receive at least one fraction of radiotherapy. Incorporating a 10% non-evaluable rate gives a target sample size of 62 patients (31 in each planning group).

The numbers and proportions of patients with acute non-GU CTCAE V.4 toxicity >grade 3 within the first 3 months of completing radiotherapy in each planning method will be presented together with 95% one-sided exact CIs (the 90% two-sided CI will also be presented).

Late toxicity will be summarised by frequencies and proportions at each time point by treatment group. Kaplan-Meier methods will be used to present time to event outcomes; due to small numbers, no formal comparison is planned.

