## Materials and analysis

### Study design

HYBRID is a non-blinded multicentre non-comparative randomised control phase II trial conducted in accordance with the Research Governance Framework for Health and Social Care and principles of Good Clinical Practice. The trial is sponsored by The Institute of Cancer Research, registered on the ClinicalTrials.gov database and is included in the National Institute for Health Research (NIHR) Clinical Research Network portfolio. The final ethics approved version of HYBRID trial protocol is provided in the online supplementary file 1.

10.1136/bmjopen-2020-037134.supp1Supplementary data

All patients are planned to receive a total dose of 36 Gy in 6-weekly fractions randomised (1:1) between treatment delivered using a single standard plan (control) or adaptive radiotherapy using a library of plans. Randomisation takes place centrally by the trials unit (Clinical Trials and Statistics Unit at The Institute of Cancer Research (ICR-CTSU)) within a maximum of 6 weeks prior to the planned radiotherapy start date.

The primary endpoint is to evaluate acute non-GU grade 3 or greater toxicity as assessed using Common Terminology Criteria for Adverse Events (CTCAE V.4). The secondary endpoints are to assess local disease control at 3 months, control rate of presenting symptoms as measured by CTCAE V.4, patient-reported outcomes as measured by Inflammatory Bowel Disease Questionnaire, King’s Health Questionnaire and EQ5D, late toxicity as measured by CTCAE V.4 and the Radiation Therapy Oncology Group (RTOG) late radiation morbidity scoring schema, time to local disease progression, overall survival and proportion of fractions benefiting from adaptive planning.

The trial has a number of exploratory secondary endpoints related to the appropriate identification of plan selection, target coverage and concordance between clinical and patient-reported outcomes.

Figure 1 shows the trial schema and overview of follow-up. Table 1 provides summary of the scheduled prerandomisation, on treatment, and post-treatment assessments.

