**Figure 1 F1:**
[figure not shown]
Trial schema. RTOG, Radiation TherapyOncology Group.

**Table 1 T1:** Schedule of assessments

Visit/assessment	Prerandomisation	Up to 14 days pretreatment	On treatment (before each fraction)	4 weeks after completion of radiotherapy	3 months after completion of radiotherapy	6 months after completion of radiotherapy	12 months after completion of radiotherapy	24 months after completion of radiotherapy	Annually thereafter
Histological confirmation of bladder cancer	X								
Radiological assessment of bladder cancer (minimum CT abdomen and pelvis and chest X-ray)	X*								
Acute toxicity assessment (CTCAE V.4)		X	X	X	X				
Full blood count, urea and electrolytes		X	X†						
Patient-reported outcomes questionnaire (IBDQ, KHQ and EQ5D)		X	X‡		X	X			
Cystoscopy under general anaesthetic with tumor bed biopsy (*if not possible, flexible cystoscopy with visual inspection of tumor bed and urine cytology*)					X				
Late toxicity assessment (CTCAE V.4 and RTOG)						X	X	X	
Flexible cystoscopy with visual inspection of tumor bed (*if not possible, urine cytology and pelvic CT scan*)						X	X		
Assessment of disease status								X	X

*Baseline radiological assessment should take place ideally within 4 weeks and within a maximum of 6 weeks prior to randomisation.

†Full blood count, urea and electrolytes prior to fractions 2, 4 and 6 only.

‡PRO questionnaire at fraction 6 only.

CTCAE, Common Terminology Criteria for Adverse Events; IBDQ, Inflammatory Bowel Disease Questionnaire; KHQ, King’s Health Questionnaire; RTOG, Radiation Therapy Oncology Group.

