### Safety reporting

Data are collected at each trial visit regarding any adverse events according to the CTCAE V.4.0 grading system. The highest grade observed since the last visit should be reported. All serious adverse events (SAEs) are reported to the ICR-CTSU within 24 hours of the PI becoming aware of the event. SAEs should be followed up until clinical recovery is complete or until the condition has stabilised. Any safety concerns will be reported to the main research and ethics committee by ICR-CTSU as part of the annual progress report.

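### The late CTCAE proportions at 6, 12 and 24 months are worst grades over 3, 6 and 12 months, so for transient toxicity a constant rate can look like a rise

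*Protocol article*

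**What the plan says.** Three parts of the protocol article bear on this point.

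- **Recording.** Safety reporting says "Data are collected at each trial visit regarding any adverse events according to the CTCAE V.4.0 grading system", and then "The highest grade observed since the last visit should be reported". The article gives no other recall rule for CTCAE grades.
- **Schedule.** Table 1 (Study design) marks late toxicity, on CTCAE and RTOG, at 6, 12 and 24 months after radiotherapy. The visit before the first of these is the one "3 months after completion of radiotherapy". No visit falls between 12 and 24 months.
- **Analysis.** Statistical considerations says "Late toxicity will be summarised by frequencies and proportions at each time point by treatment group". No other late-toxicity summary is described. On time-to-event outcomes the same paragraph adds that "due to small numbers, no formal comparison is planned".

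Late toxicity is a named secondary endpoint in Study design: "late toxicity as measured by CTCAE V.4 and the Radiation Therapy Oncology Group (RTOG) late radiation morbidity scoring schema".

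**The concern.** A proportion at a time point is naturally read as the share of patients affected at that time. Under the recording rule, the CTCAE proportion is instead the share who reached a given grade at any time since the previous visit, and that look-back period doubles from one late visit to the next. For effects that come and go, a longer look-back catches more patients even if nothing has changed biologically.

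At stake is the reading over time. Whether late effects settle or accumulate is a natural question for a schedule that, according to the Introduction, has had no prospective multicentre assessment. The descriptive table is the only late-toxicity result described, so nothing else in the article would correct a misreading of it.

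**Working it through.** **Plan's own figures.** The article gives no late-toxicity rate to reproduce. Its primary design does reproduce and does not depend on this point. Accepting a technique when 24 or more of 28 patients are free of toxicity gives an exact one-sided alpha of 0.047 (p0 = 0.7) and power of 0.858 (p1 = 0.9).

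**Look-back windows (Table 1).** 6 − 3 = 3 months; 12 − 6 = 6 months; 24 − 12 = 12 months.

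**Brief episodes, constant hazard.** The article gives no late event rate, so the hazard h per patient-year is an assumption, shown over a range. The probability of at least one episode in a window of m months is 1 − exp(−h·m/12).

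| Assumed h | 6-month visit (m = 3) | 12-month visit (m = 6) | 24-month visit (m = 12) |
|---|---|---|---|
| 0.05 | 1.2% | 2.5% | 4.9% |
| 0.10 | 2.5% | 4.9% | 9.5% |
| 0.20 | 4.9% | 9.5% | 18.1% |

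For h = 0.10 the exponents are 0.025, 0.05 and 0.10. The ratio of last to first is 9.5/2.5 = 3.8, and the ceiling for rare, brief events is 12/3 = 4.

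The table also shows the converse. If the hazard halves at each interval (0.20, then 0.10, then 0.05), the exponent is 0.05 each time and all three columns show 4.9%. A real improvement would then look flat.

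**Episodes that last.** The size depends on duration. Take a stable process with constant prevalence π and mean episode duration D months (both assumed). The probability of being affected at any time in a window of m months is 1 − (1 − π)·exp(−m·π/((1 − π)·D)). With π = 10%:

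| Mean duration D | 6-month visit | 12-month visit | 24-month visit | Last / first |
|---|---|---|---|---|
| 3 months | 19.5% | 27.9% | 42.3% | 2.2 |
| 12 months | 12.5% | 14.9% | 19.5% | 1.6 |
| 60 months | 10.5% | 11.0% | 12.0% | 1.1 |

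Status at the visit would be 10% throughout. For permanent toxicity with no new cases the columns are equal and the artefact disappears.

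**In patients.** With 31 per group and nobody lost, 2.5%, 4.9% and 9.5% are about 0.8, 1.5 and 2.9 patients.

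**The case against.** The strongest reply is that the article promises no time trend. It plans a display by group, and both groups share one visit schedule, so the arms remain comparable at each visit. That stands. A reader might infer that the comparison of planning methods is biased, and the documents do not support that.

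Second, the recall rule sits under Safety reporting, and the full protocol or an analysis plan may define the late-toxicity table differently. This lowers certainty but does not remove the point. The rule is worded for CTCAE data at every trial visit, late visits are trial visits, and the article sets time-point wording beside interval data.

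Third, late radiation effects may persist, and then the distortion is small. This also stands. The near four-fold figure is the upper end of a range that runs down to no rise.

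Fourth, counts will be small. The Introduction reports about 20% survival beyond 24 months in an earlier trial of lower-dose schedules. If that applied here (an assumption), about 0.2 × 31 = 6 patients per group would reach the last visit, and 9.5% of them is about 0.6 of a patient. Noise could then hide the artefact, which is a further reason not to read a trend across the columns.

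A reader might also infer that the CTCAE and RTOG columns cannot be compared because RTOG is scored as status at the visit. The article gives no recall period for RTOG, so this cannot be concluded.

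**Conclusion.** The point holds for late CTCAE grades and for reading them over time. As written, the by-visit proportions are period maxima over 3, 6 and 12 months. For transient or recurrent toxicity, a constant rate can appear as a rise of up to about four-fold for brief episodes and close to none for long-lasting toxicity. This rests on the Safety reporting rule governing the late visits. The sizes rest on assumed rates and durations, since the article gives none.

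It would go too far to say that the proportions must rise whatever the toxicity, or that the trial's main conclusion is at risk. Comparison between arms at a visit, the primary endpoint, the sample size and the decision rule are unaffected. This is a modest, inexpensive correction to a descriptive secondary endpoint.

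**What to change.** In Statistical considerations:

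1. Add the cumulative proportion of patients with a first grade 3 or higher late CTCAE event by 6, 12 and 24 months, by planning group. Account for death and loss to follow-up, for example with death as a competing event. This can be built from the worst grade in each interval.
2. Keep the by-visit CTCAE table, but label its columns 3–6, 6–12 and 12–24 months, and state that they are not to be read as a time trend.

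Dividing the interval proportions by window length is not a safe substitute. The rule yields a worst grade per interval, not counts of new events. Persistent toxicity recorded in a constant 10% of patients would become −ln(0.9) divided by 0.25, 0.5 and 1 year, that is 0.42, 0.21 and 0.105 per patient-year, a spurious four-fold fall.

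The cost is analysis wording and one extra descriptive table based on small numbers. No new visits, patients or data are needed.

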## Abstract

**Introduction:**

Patients with muscle invasive bladder cancer (MIBC) who are unfit and unsuitable for standard radical treatment with cystectomy or daily radiotherapy present a large unmet clinical need. Untreated, they suffer high cancer specific mortality and risk significant disease-related local symptoms. Hypofractionated radiotherapy (delivering higher doses in fewer fractions/visits) is a potential treatment solution but could be compromised by the mobile nature of the bladder, resulting in target misses in a significant proportion of fractions. Adaptive ‘plan of the day’ image-guided radiotherapy delivery may improve the precision and accuracy of treatment. We aim to demonstrate within a randomised multicentre phase II trial feasibility of plan of the day hypofractionated bladder radiotherapy delivery with acceptable rates of toxicity.

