## Introduction

Standard radical management of muscle invasive bladder cancer (MIBC) involves either radical cystectomy or a course of daily radiotherapy delivered with radiosensitisation over 4–7 weeks.^1–5^ Given the aetiological association of bladder cancer with smoking, cardiovascular and respiratory comorbidities are common.^6 7^ Undertreatment and poor access to effective treatment are particularly evident in older patient groups who have the highest risk of cancer related morbidity and death from initially curable bladder cancer.^8^

Hypofractionated radiotherapy (delivering higher doses in fewer fractions/visits) may provide a potential treatment solution for these patients. The only multicentre randomised control trial of hypofractionated bladder radiotherapy investigated two schedules of relatively low biological effectiveness; 35 Gy in 10 fractions over 2 weeks and 21 Gy in 3 fractions over 1 week.^9^ Both treatment groups achieved similar symptom control with no significant difference in efficacy or toxicity evident between different radiotherapy schedules. Despite the palliative treatment intent, approximately 20% of patients achieved survival beyond 24 months.^9^ Given the presumed dose–response relationship of MIBC to radiotherapy, a higher biological effective dose would be expected to improve local disease and symptom control further.^10^

A number of small single-centre studies using the higher biological dose of 30–36 Gy in 6 Gy per fraction suggest acceptable acute and late toxicity with local control achieved in over of 60% patients at 3 months.^11–13^ Prospective multicentre assessment of this radiotherapy schedule has not yet been performed.

Reliably targeting the bladder for radiotherapy is challenging. It is a relatively mobile structure subject to marked shape and volume change during a course of radiotherapy.^14–16^ This has meant that historically bladder cancer radiotherapy has been delivered with some element of geographical miss (up to 57% of fractions) even when large safety margins of upto 1.5 cm are applied to create the planning target volume (PTV).^17^ The expected consequence of dose intended for the target hitting adjacent normal structures is reduced tumor control and increased treatment related toxicity. Larger safety margins would more reliably encompass the bladder target variation but would further increase the normal tissue exposed to radiation dose, so increase side effects from treatment.

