### Participants and eligibility

Target recruitment is 62 patients from 14 participating UK centres. Patients with histological confirmation of invasive bladder cancer (T2-T4aN0M0) of any pathological subtype unsuitable for radical cystectomy or radical daily radiotherapy for any reason including but not limited to performance status, comorbidity or patient refusal will be approached for inclusion. Eligible patients would have an expected survival of greater than 6 months, be willing to accept assessment with cystoscopy following radiotherapy completion and be able to attend for follow-up.

Patients with an indwelling urinary catheter, active or history of other malignancy within 2 years of randomisation except for non-melanomatous skin carcinoma, previous non-muscle invasive bladder tumors and low-risk prostate cancer (as defined by National Comprehensive Cancer Network (NCCN) risk stratification as T1/T2a, Gleason 6 PSA <10) will be excluded. Those with history of radiation to the pelvis or other contraindication to pelvic radiotherapy, for example, inflammatory bowel disease will also be excluded.

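### Kaplan-Meier is the only method named for time to local progression, and it does not estimate the probability of local failure when deaths without progression are likely to be common

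*Protocol article*

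**What the plan says.** Statistical considerations gives one rule for every time-to-event outcome: "Kaplan-Meier methods will be used to present time to event outcomes; due to small numbers, no formal comparison is planned". Study design closes its list of secondary endpoints with "time to local disease progression, overall survival and proportion of fractions benefiting from adaptive planning", so local progression and survival are two separate outcomes under one method. Local disease control at 3 months appears in the same list as an endpoint of its own.

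On mortality, the Abstract says of these patients: "Untreated, they suffer high cancer specific mortality and risk significant disease-related local symptoms". Participants and eligibility adds: "Eligible patients would have an expected survival of greater than 6 months". The only survival figure is in the Introduction, for the two earlier palliative schedules, where "approximately 20% of patients achieved survival beyond 24 months".

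The article does not say whether a patient who dies without local progression is censored or counted as having the event. It mentions neither competing risks nor cumulative incidence.

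**The concern.** Kaplan-Meier suits overall survival, where death is the event. For local progression it estimates a probability of failure only if censored patients could still fail later at the same rate as those who remain under observation. A patient who has died cannot progress locally. Censoring that patient assigns to the dead the later failures of the survivors, so the failure curve rises too high. The more deaths there are, the larger the excess.

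The trial enrols people for whom radical treatment is unsuitable, with performance status and comorbidity among the reasons given. Follow-up of disease status extends to 24 months and yearly thereafter, so many patients may die before they could be seen to progress.

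The Introduction justifies the higher-dose schedule partly by an expected gain in local control. In a non-comparative trial, each group's absolute estimate is what readers will take away, and this bias acts on the absolute estimate.

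**Working it through.** **The plan's own figures.** The article gives no figure for time to local progression. Its sample size reproduces: with 28 evaluable patients and at least 24 free of toxicity required, the exact one-sided alpha is 0.0474 at p0 = 0.7 and power is 0.858 at p1 = 0.9. An allowance of 10% gives 28 × 1.10 = 30.8, so 31 per group and 62 in total. None of this depends on how local progression is analysed.

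**Inputs for the illustration (assumptions, except where stated)**
- Constant cause-specific hazards: hl for local progression, hd for death without local progression.
- 1 minus Kaplan-Meier at 24 months, deaths censored: 50% or 30%. The article has no 24-month figure.
- Freedom from death without progression at 24 months: 20%, 40% or 60%. The 20% end is borrowed from the survival figure in the Introduction. The other values are assumed.

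**Formulas**
- 24·hl = −ln(1 − failure estimate): 0.6931 for 50%, 0.3567 for 30%.
- 24·hd = −ln(proportion free of death without progression): 1.6094 for 20%, 0.9163 for 40%, 0.5108 for 60%.
- Cumulative incidence at 24 months = hl/(hl + hd) × [1 − exp(−24(hl + hd))].

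**Worked example (50% failure estimate, 20% free of death without progression).** 0.6931/(0.6931 + 1.6094) = 0.301. exp(−2.3026) = 0.5 × 0.2 = 0.10. Cumulative incidence = 0.301 × 0.90 = 0.271.

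| 1 − Kaplan-Meier at 24 months | Free of death without progression | Cumulative incidence | Excess (points) |
|---|---|---|---|
| 50% | 20% | 27.1% | 22.9 |
| 50% | 40% | 34.5% | 15.5 |
| 50% | 60% | 40.3% | 9.7 |
| 30% | 20% | 15.6% | 14.4 |
| 30% | 40% | 20.2% | 9.8 |
| 30% | 60% | 23.8% | 6.2 |

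**If deaths count as events instead.** The curve then shows freedom from both events, and its complement is 1 − (1 − failure estimate) × (proportion free of death without progression). In the 50% rows this is 1 − 0.5 × 0.2 = 90% to 1 − 0.5 × 0.6 = 70%. In the 30% rows it is 1 − 0.7 × 0.2 = 86% to 1 − 0.7 × 0.6 = 58%. These are progression-free survival figures and are far from the incidence of local failure.

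**The case against.** **Censoring of deaths is not stated.** The event and censoring rules may stand in the full protocol or analysis plan, neither of which is shown. This objection stands in part. A reader might infer that the trial will overstate local failure, but the document does not support that as a fact, and the overstatement is conditional on censoring. The objection does not rescue the stated method, because the other usual choice, counting deaths as events, changes the endpoint to progression-free survival.

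**The mortality anchor is weak.** The 20% is all-cause survival under schedules that the article describes as biologically less effective. It is not freedom from death without progression. Some deaths will follow progression and do not compete with it, and eligibility also admits patients who refuse radical treatment. This stands. It is why the 20% end is read as an upper bound on the bias and why a range is shown.

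**The consequence is limited.** The outcome is secondary and descriptive, with no formal comparison. This stands too, although a descriptive estimate should still estimate what its name says.

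**Two wider readings are tempting but unsupported.**
- A reader might extend the point to local control in general. Local control at 3 months is a separate endpoint, assessed at a fixed visit by cystoscopy, and need not involve Kaplan-Meier. No secondary endpoint is designated as key.
- A reader might also fault the late-toxicity plan: "Late toxicity will be summarised by frequencies and proportions at each time point by treatment group". A table by visit at 6, 12 and 24 months is ordinary description. The denominator is merely unstated. Safety reporting asks for the worst grade since the previous visit, so a patient who reports a severe event and later dies remains in the count for the visit at which it was reported. The table is not an error.

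**Conclusion.** The point holds for time to local progression alone. Whichever usual way deaths are handled, Kaplan-Meier will not give the incidence of local failure in this population. If deaths are censored, the overstatement at 24 months is about 6 to 23 percentage points over the assumed ranges, with the largest value at the borrowed 20% end. These sizes rest on constant hazards and on assumed failure and death rates. The direction of the bias, given censoring, does not depend on those values. The matter is worth correcting before results are reported, but it does not touch the trial's decision rule.

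**What to change.** - Keep Kaplan-Meier for overall survival.
- Present time to local progression in each planning group as cumulative incidence by the Aalen-Johansen estimator, with death without local progression as a competing event.
- State explicitly that such deaths are neither censored nor counted as progression.
- Optionally, add the cumulative incidence of first grade 3 or greater late toxicity, with death as a competing event, beside the table by visit.

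The cost is a sentence or two in the analysis plan and a few lines of code. Disease status and survival are already followed for the listed endpoints, so no new data are needed. Because recruitment is complete, the change affects analysis and reporting only.
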